### Study population

The study aims to recruit 200 patients over the age of 60 years admitted to Northern Hospital with fractured neck of femur who are planned to undergo surgery within 48 hours.

### Inclusion criteria

Patients may be included in the trial if they are over 60 years of age and have a NOF fracture with surgical treatment planned for within the next 48 hours.

### Exclusion criteria

Patients who meet any of the following criteria will be excluded from the study: 1) current ivabradine use, current atorvastatin use of 80 mg daily, 3) heart rate <65 bpm prior to randomization, 4) known liver disease or liver enzymes more than three times the higher limit of normal, 5) preoperative troponin elevation, 6) artificial pacemakers, sick sinus syndrome or complete heart block, 7) concomitant CYP3A4 inhibitors (ketoconazole, macrolides, cyclosporin, gestodene and antiretrovirals), 8) significant cognitive disorders, and 9) patients who do not undergo surgical treatment for lower limb fracture for any reason. If such patients were initially enrolled they will be excluded from the analysis (per protocol analysis).

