## Methods/Design

This is a prospective, single-centre (Northern Hospital, Victoria, Australia), open-label, 2x2 factorial, randomized controlled trial of ivabradine and atorvastatin in the prevention of myocardial injury following emergent orthopedic surgery for lower limb fracture. The Northern Hospital Ethics Committee approved this study on 6 July 2012 (reference number HREC P06/12). This study complies with the Declaration of Helsinki. Informed consent will be obtained from all participating patients. Upon signing informed consent, the patient’s data will be populated as per protocol.

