### Secondary outcome measures

The secondary outcome measures will be as follows: myocardial infarction according to the universal definition [8]; death in-hospital, at 30 days and 12 months; stroke in-hospital, at 30 days and 12 months; markers of myocardial stress: NT-proBNP (pmol/L), MR-proANP (pmol/L), MR-proADM (nmol/L) and CT-proET-1 (pmol/L); and markers of plaque burden: sPLA2 and Lp-PLA2 mass (%) and activity (%). There are also several outcomes that will be monitored for safety purposes: symptomatic bradycardia or heart block requiring the cessation of ivabradine, and liver enzyme elevation more than three times the upper limits of normal (ALP, GGT, AST and ALT measured in U/L) requiring the cessation of atorvastatin.

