### Ivabradine protocol

Open-label ivabradine will be administered according to the following protocol.

Heart rate 65 to 90 bpm at randomization: starting dose of 5.0 mg administered orally twice daily commencing immediately after randomization (within two hours and prior to surgery) and continued until discharge. Heart rate >90 bpm at randomization: starting dose of 7.5 mg administered orally twice daily commencing immediately after randomization (within two hours and prior to surgery) and continued until discharge. ivabradine dose and heart rate will be reviewed on a daily basis by the cardiology research fellow (associate investigator) and adjusted as follows: 1) if heart rate remains over 65 bpm during treatment then ivabradine dosage will be increased by 2.5 mg twice daily to a maximum of 7.5 mg twice daily; 2) if heart rate falls below 50 bpm during treatment then ivabradine dosage will be reduced by 2.5 mg twice daily; and finally 3) if heart rate remains below 50 bpm on ivabradine 2.5 mg twice daily then ivabradine will be ceased.

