### Atorvastatin protocol

Open-label atorvastatin will be administered according to the following protocol. A dosage of 80 mg administered orally daily will commence immediately after randomization (within two hours and prior to surgery) and will continue until discharge (unless otherwise indicated according to history and lipid profile). A liver function test and creatinine kinase levels will be monitored to assess side effects.

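### The only stated analysis set drops enrolled patients who are not operated on, although both open-label drugs start before surgery and death, stroke and safety need no operation to be observed

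*Protocol article*

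**What the plan says.** Under Inclusion criteria, a patient must "have a NOF fracture with surgical treatment planned for within the next 48 hours". Surgery is an intention at that point, not a fact.

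Under Exclusion criteria, item 9 is "patients who do not undergo surgical treatment for lower limb fracture for any reason", followed by the rule "If such patients were initially enrolled they will be excluded from the analysis (per protocol analysis".

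Both study drugs begin before the operation. The Ivabradine protocol has dosing "commencing immediately after randomization (within two hours and prior to surgery) and continued until discharge". The Atorvastatin protocol says treatment "will commence immediately after randomization (within two hours and prior to surgery". Methods/Design describes an "open-label, 2x2 factorial, randomized controlled trial of ivabradine and atorvastatin", and the control group receives no study drug.

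The Primary outcome measure is peak troponin I over postoperative days 1 to 4. The Secondary outcome measures include death and stroke in hospital, at 30 days and at 12 months. The events monitored for safety include "symptomatic bradycardia or heart block requiring the cessation of ivabradine".

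The Statistical analysis section names no analysis population, and no all-randomised or intention-to-treat analysis is mentioned elsewhere. The sentence in the Exclusion criteria is the only statement of who is analysed.

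**The concern.** Item 9 sits in the eligibility list but cannot work as an eligibility criterion. Whether a patient is operated on is generally known only after allocation, and usually after the first dose. Removing patients on that basis selects on a post-randomisation event.

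That is harmless only if non-operation is unrelated to allocation, and the protocol does not secure this. It foresees drug effects that could bear on fitness for surgery, and those who decide whether to cancel may know the arm. The exclusion covers every reason for non-operation, so preoperative death and deterioration fall within it.

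Death, stroke and safety events are defined for every randomised patient. If someone dies or develops heart block between the first dose and the planned operation, the rule as worded takes that patient out of the arm in which it happened. Randomisation then no longer protects the comparison, and early harm may be under-counted.

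**Working it through.** **1. Order of events, from the protocol's own sections.** Surgery planned within 48 hours (Inclusion criteria) → randomisation → first dose within two hours and before surgery (Ivabradine and Atorvastatin protocols) → surgery takes place or does not → exclusion if it does not (Exclusion criteria). The exclusion comes after allocation and, normally, after exposure.

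**2. The protocol's own power figures.** Inputs from Sample size calculation: f = 0.25, alpha 0.05, four groups, power 0.90, calculated N 171, planned N 200, stated power 0.94. Method: noncentral F with λ = f²N, 1 numerator df and N − 4 denominator df.
- N = 171: λ = 0.0625 × 171 = 10.69; power 0.902, and 171 is the smallest N reaching 0.90.
- N = 200: λ = 0.0625 × 200 = 12.5; power 0.940.

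Both stated figures reproduce. Assumed exclusions of 2%, 5%, 10% and 15% leave 196, 190, 180 and 170 patients, with power 0.936, 0.929, 0.916 and just under 0.900. The margin is 200 − 171 = 29 patients, or 29/200 = 14.5%.

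**3. Illustration for death at 12 months.** The Background reports 52.9% troponin-positive in an earlier urgent orthopaedic cohort, with 12-month mortality of 37% in positive and 2.1% in negative patients: 0.529 × 37% + 0.471 × 2.1% = 20.6%. I take 20 deaths per 100. Assumptions: one drug margin of 100 v 100, no true drug effect (true RR 1.00), and k preoperative deaths dropped from the drug group and none from control. Then RR = [(20 − k)/(100 − k)] ÷ (20/100).

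| k | Drug group after exclusion | Spurious RR |
|---|---|---|
| 1 | 19/99 = 0.192 | 0.96 |
| 2 | 18/98 = 0.184 | 0.92 |
| 5 | 15/95 = 0.158 | 0.79 |

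The last row is extreme. At a constant yearly hazard, 20 deaths would put about 20 × 2/365 = 0.11 in a 48-hour window. The true early hazard is probably higher, but nothing in the protocol supports 5 against 0.

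**4. Illustration for troponin positivity.** Assumptions, none of them in the protocol except the 52.9%: no drug effect; overall event rate 52.9%; a high-risk fifth of patients with event rate h between 0.70 and 0.90; all excluded patients high-risk; 100 v 100. If a fraction e of an arm is excluded, the rate left is (0.529 − e·h)/(1 − e).
- Equal exclusion (2% v 2% or 5% v 5%): difference 0.
- 2% control v 5% drug: h = 0.70 gives 0.5200 − 0.5255 = −0.6 points; h = 0.90 gives 0.5095 − 0.5214 = −1.2 points. Type I error 0.051 to 0.053.
- 2% control v 10% drug: h = 0.70 gives 0.5100 − 0.5255 = −1.6 points; h = 0.90 gives 0.4878 − 0.5214 = −3.4 points. Type I error 0.055 to 0.075.

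On the primary outcome the bias stays small unless exclusions are frequent and clearly unequal.

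**The case against.** The strongest defence concerns the primary outcome. Peak troponin over postoperative days 1 to 4 does not exist without an operation, so a set restricted to operated patients is a natural choice. That stands in part: such a set is defensible as modified intention-to-treat if the decision not to operate cannot depend on allocation. With open-label drugs given beforehand and an exclusion covering every cause, the protocol does not ensure that condition. The defence does not extend to death, stroke or safety.

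Several stronger readings are tempting, and the document does not support them.
- A reader might infer that the plan expressly deletes deaths, strokes and safety events. It does not name them. The rule speaks only of the analysis, safety events are to be monitored without a surgery condition, and the Follow-up protocol covers all patients to one year. The fair statement is that the exclusion is not limited to troponin.
- A reader might think delayed surgery triggers exclusion. It does not; only patients never operated on are removed.
- A reader might take the risk ratio of 0.79 as an expected size. It needs five preoperative deaths on drug and none on control. The mortality behind it also comes from patients who did undergo surgery, and this trial excludes preoperative troponin elevation, so the rate may not carry over.
- A reader might see a power problem. On the protocol's own calculation, 29 patients can be lost before power falls below 0.90.

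**Conclusion.** The point holds as a matter of validity. The protocol fixes, rather than leaves open, an analysis set that depends on a post-randomisation event which open-label treatment could influence, and it does not confine that set to the outcome for which surgery is necessary. A separate analysis plan might add an all-randomised analysis, but the rule in the protocol would still need to be changed to agree with it.

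The size of the bias cannot be derived, because no non-operation rate is given. It is nil if exclusions are equal and unrelated to arm. Under the stated assumptions the spurious risk ratio for death is 0.96 or 0.92 with one or two one-sided preoperative deaths, and 0.79 in the extreme case. For troponin positivity it is roughly 1 to 3 percentage points when exclusions are unequal. The case for change rests on the low cost of removing the risk, not on a demonstrated large bias.

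**What to change.** 1. Remove item 9 from the eligibility list, together with the sentence that drops such patients from the analysis.
2. State that death, stroke and the safety outcomes are analysed in all randomised patients by allocated arm.
3. Report the number of patients not operated on, with reasons, by arm.
4. For postoperative troponin, define the main set as operated patients analysed as allocated and call it modified intention-to-treat, not per protocol. Add a sensitivity analysis with all randomised patients, for example counting preoperative death or myocardial injury as an event. Imputing a postoperative troponin for someone never operated on would change the question being asked and is not needed here.

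Cost: a wording change and one extra analysis set. Follow-up to one year is already planned for all patients. The all-randomised analyses will be slightly diluted by the patients who never had surgical stress.

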### Randomization protocol

Patients will be randomized using a computerized block randomization method with blocks of variable sizes to ensure ‘true’ randomization and equal numbers in each treatment group. Patients will be randomized to one of four groups in a 1:1:1:1 ratio: no treatment (control group), atorvastatin 80 mg daily, ivabradine twice daily (as per protocol), or ivabradine twice daily (as per protocol) and atorvastatin 80 mg daily.

### Ivabradine protocol

Open-label ivabradine will be administered according to the following protocol.

Heart rate 65 to 90 bpm at randomization: starting dose of 5.0 mg administered orally twice daily commencing immediately after randomization (within two hours and prior to surgery) and continued until discharge. Heart rate >90 bpm at randomization: starting dose of 7.5 mg administered orally twice daily commencing immediately after randomization (within two hours and prior to surgery) and continued until discharge. ivabradine dose and heart rate will be reviewed on a daily basis by the cardiology research fellow (associate investigator) and adjusted as follows: 1) if heart rate remains over 65 bpm during treatment then ivabradine dosage will be increased by 2.5 mg twice daily to a maximum of 7.5 mg twice daily; 2) if heart rate falls below 50 bpm during treatment then ivabradine dosage will be reduced by 2.5 mg twice daily; and finally 3) if heart rate remains below 50 bpm on ivabradine 2.5 mg twice daily then ivabradine will be ceased.

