Postoperative atrial fibrillation (AF) is common both after cardiothoracic and non-cardiothoracic surgery [31]. In patients undergoing non-cardiothoracic surgery, the reported incidence of postoperative AF is as high as 12% [32], and has not been documented in an emergent orthopedic surgery group where the incidence may be higher given the typically elderly population. Postoperative AF can be observed throughout the postoperative course, with a peak on the second postoperative day [33]. Even though postoperative AF can be self-limiting, it may be associated with hemodynamic derangements, postoperative stroke, PMI, ventricular arrhythmias and heart failure [34, 35]. In many reports, development of postoperative AF is associated with a longer hospital stay, greater morbidity and mortality and increased costs [33, 36]. The pathophysiology of postoperative AF is not well understood, however right atrial overdistension and myocardial stretch in response to catecholamine release may play a significant role [37].

Ivabradine (Coralan™) is an orally bioavailable, specific inhibitor of the I_*f*_ current in the sinoatrial node [38]. It is a pure heart rate lowering agent in patients with sinus rhythm, but unlike beta-blockers it has no effect on blood pressure [39, 40], myocardial contractility [41], intracardiac conduction or ventricular repolarization [42]. Ivabradine could potentially provide the perioperative benefits of beta-blockers without the detrimental effects of hypotension, leading to improved outcomes and reduced adverse cardiovascular events in the postoperative period. A small series case study of 15 patients showed that ivabradine does attenuate catecholamine induced tachycardia following cardiac surgery, with positive effects on cardiac index, stroke volume index and mean arterial pressure [43]. A small (n = 111) non-randomized study of ivabradine in patients undergoing carotid endarterectomy found that ivabradine therapy (n = 33) reduced PMI compared to patients not receiving any beta-blockers or ivabradine [44]. No randomized studies with ivabradine in patients undergoing cardiac or non-cardiac surgery have been performed to date.

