### Electrocardiography protocol

A digital 12-lead ECG will be recorded preoperatively and on postoperative days 1, 2 and 3 and assessed for heart rate, PR interval, QRS duration and morphology, Q waves, QT duration and QTc, as well as ST-T morphology and overall interpretation to look for changes that meet the universal definition of myocardial infarction.

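### Patients in atrial fibrillation at entry can be randomized to ivabradine, although the protocol ties the drug's rate lowering, the mechanism under test, to sinus rhythm

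*Protocol article*

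**What the plan says.** The Background section on myocardial stress says of ivabradine: "It is a pure heart rate lowering agent in patients with sinus rhythm". The same sentence denies any effect on "intracardiac conduction or ventricular repolarization". The Discussion gives the hypothesis: ivabradine will lower the rate and magnitude of perioperative myocardial infarction by reducing heart rate.

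The Inclusion criteria ask for age over 60 and a femoral neck fracture with surgery planned within 48 hours. They set no rhythm condition. The Exclusion criteria contain one rate rule, "heart rate <65 bpm prior to randomization", and one rhythm and conduction rule, "artificial pacemakers, sick sinus syndrome or complete heart block". AF is not listed.

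The Ivabradine protocol sets the starting dose by heart rate: 5.0 mg twice daily at 65 to 90 bpm, and above that, "Heart rate >90 bpm at randomization: starting dose of 7.5 mg administered orally twice daily". The first adjustment step reads: "if heart rate remains over 65 bpm during treatment then ivabradine dosage will be increased by 2.5 mg twice daily", up to 7.5 mg twice daily. The other two steps act only below 50 bpm. None mentions rhythm.

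The Electrocardiography protocol states: "A digital 12-lead ECG will be recorded preoperatively and on postoperative days 1, 2 and 3". It attaches no eligibility decision to the preoperative tracing.

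**The concern.** On the protocol's own account, sinus rhythm is a precondition for the effect being tested. A drug that slows the sinus node and leaves conduction alone is not expected to slow the ventricular rate in AF. The entry criteria already screen on rate and on some rhythm disorders, but they leave out this one.

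A patient in AF at randomization can therefore be placed in either ivabradine cell and counted as treated without the proposed mechanism being available. Because allocation is random, this does not favour either side. It averages a group with no expected effect into the ivabradine contrast and shrinks the difference. What is at stake is the chance of detecting a real ivabradine effect on the primary outcome.

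The dosing rule shares the gap in a smaller way. A rate above 65 bpm in AF triggers an increase of a drug that is not expected to change that rate.

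**Working it through.** **Inputs from the Sample size calculation.** f = 0.25, two-sided alpha 0.05, target power 0.90, calculated size 171, planned size 200 in four cells of 50, stated power 0.94. The plan's ANOVA method is used here only as a yardstick.

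**Reproducing the plan.** Noncentral F with numerator df = 1, denominator df = N − 4 and noncentrality λ = f² × N.

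- N = 171: power 0.9015, the smallest N that reaches 0.90.
- N = 200: λ = 0.0625 × 200 = 12.5, power 0.940.

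Both stated figures are reproduced. They rest on one numerator degree of freedom, that is, on a single factorial contrast such as ivabradine against no ivabradine. With df = 3 the results would be N = 231 and power 0.848.

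**Assumptions not in the document.** A share x of patients is in AF at randomization; f = 0.25 is the effect in sinus rhythm; ivabradine has no effect in AF; the within-cell spread is unchanged. The average ivabradine effect is then f′ = 0.25 × (1 − x).

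**Ivabradine main effect at N = 200, AF patients admitted.**

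| x (assumed) | f′ | λ = f′² × 200 | Power |
|---|---|---|---|
| 0 | 0.2500 | 12.50 | 0.940 |
| 5% | 0.2375 | 11.28 | 0.917 |
| 10% | 0.2250 | 10.13 | 0.886 |
| 20% | 0.2000 | 8.00 | 0.804 |

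Power falls to the 0.90 target at x = 7.9%.

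**AF patients excluded.**

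| x (assumed) | Not replaced: N = 200(1 − x) | Power, either contrast | Replaced to 200: power | Otherwise eligible patients needed, 200/(1 − x) |
|---|---|---|---|---|
| 5% | 190 | 0.929 | 0.940 | 211 |
| 10% | 180 | 0.916 | 0.940 | 223 |
| 20% | 160 | 0.882 | 0.940 | 250 |

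Without replacement, ivabradine power rises by 0.012, 0.029 or 0.078 against admitting AF patients (for example 0.929 − 0.917). Atorvastatin power, which AF at entry does not dilute, falls from 0.940 to 0.929, 0.916 or 0.882. Replacement to 200 avoids that loss.

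**The case against.** The strongest reply is that the size is assumed. The document gives no AF share at randomization and does not say that f = 0.25 refers to sinus rhythm. If it was meant as an average over all comers, nothing is lost. At 5% to 10% the loss is small, and the rounding up from 171 to 200 absorbs a share of up to 7.9%. All of this stands, and it is why the power figures are illustration only.

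A second reply is that exclusion costs the atorvastatin contrast patients. That is true if they are not replaced. The Trial status section says recruitment continues until 200 are enrolled, so replacement is the natural course.

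A third is that broad entry may be intended, or that daily review by the cardiology research fellow deals with AF. The document does not state such an intention, and the exclusion below 65 bpm points to a mechanism-driven trial. The printed adjustment steps refer only to heart rate, and review after randomization cannot reverse the allocation of a patient already in AF.

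Four stronger readings are tempting, and the document does not support them:

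- **The 12% as the share affected.** The Background cites postoperative AF of up to 12% after non-cardiothoracic surgery and adds, for emergent orthopedic patients, "where the incidence may be higher given the typically elderly population". That is new AF after surgery, not AF at randomization. Nor does 12 in 100 count the patients whose dose would be raised: some would already be at 7.5 mg and some would not be above 65 bpm.
- **Harm from the dosing rule.** None is shown. The increase is one 2.5 mg step to a ceiling open to every ivabradine patient. Postoperative AF is described as possibly self-limiting, so the drug may act again once sinus rhythm returns.
- **Gaps in the stopping rules.** Bradycardia and heart block appear under Secondary outcome measures as safety outcomes to be monitored. That is not a complete list of stopping rules, so the absence of AF there shows little.
- **Bias or a false positive.** Randomization protects against both. The expected direction is toward no effect.

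**Conclusion.** The point holds for eligibility. The protocol limits ivabradine's rate lowering to sinus rhythm, tests whether rate lowering prevents myocardial injury, and admits patients in AF. This is a printed criterion fixed badly, not a detail left to another document. The consequence is dilution of the ivabradine contrast; the atorvastatin contrast is untouched as the plan stands.

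The size is unknown. Under the stated assumptions it is modest at 5% to 10% AF and notable only at 20%, the top of the assumed range. A reader should not take a power shortfall as established. The dosing rule is a secondary remark: the logic is inconsistent, but the number of patients affected cannot be derived. Because the remedy is specific and cheap, the change should be made.

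**What to change.** Add an exclusion criterion: not in sinus rhythm on the preoperative 12-lead ECG, read before randomization. Keep recruiting until 200 are randomized, so that both contrasts retain power 0.94 under the plan's assumptions.

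As a minor addition, make the first adjustment step of the Ivabradine protocol conditional on rhythm: increase by 2.5 mg twice daily if the patient is in sinus rhythm and the rate remains over 65 bpm; a rate above 65 bpm in AF does not trigger an increase.

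Keep patients who develop AF after randomization in the primary analysis.

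**Cost.** One criterion and one condition. No new test is needed, but the planned preoperative ECG must be read before allocation. The population becomes narrower and recruitment somewhat slower: 11, 23 or 50 more otherwise eligible patients at an assumed 5%, 10% or 20% AF (211, 223 or 250 minus 200), at a single centre.
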